**Legend:**

**eTable 1:** Incidence of COVID-19 after post exposure prophylaxis with HCQ and placebo in participants  
in whom RTPCR could be performed

**eTable 2:** COVID-19 related symptoms of the study population

eTable 1: Incidence of COVID-19 after post exposure prophylaxis with HCQ and placebo in participants in whom RTPCR could be performed

| Outcomes (N=1156)                     | Placebo/Control group (N=587) | PEP/HCQ group (N=569) | P value |
|---------------------------------------|-------------------------------|-----------------------|---------|
| COVID-19 * (N=47)                     | 24 (4.1%)                     | 23 (4.0%)             | 0.968   |
| Definite COVID-19 a (N=37) | 21 (3.6%)                     | 16 (2.8%)             | 0.460   |
| Probable COVID-19 (N=10)              | 3 (0.5%)                      | 7 (1.2%)              | 0.187   |

\* Total absolute risk reduction was -0.1% point with number needed to treat (NNT) was 1000 and relative risk was 0.98 (95% confidence interval, 0.55 to 1.77).

a Total absolute risk reduction was -0.8% point with number needed to treat (NNT) was 125 and relative risk was 0.78 (95% confidence interval, 0.40 to 1.51).

eTable 2 : COVID-19 related symptoms of the study population

| COVID-19 symptoms  | Control group (N=594) | PEP/HCQ group (N=574) | P value |
|--------------------|-----------------------|-----------------------|---------|
| Fever (N=23)       | 13 (2.2%)             | 10 (1.7%)             | 0.583   |
| Sore throat (N=15) | 8(1.3%)               | 7(1.2%)               | 0.847   |
| Cough (N=15)       | 8(1.3%)               | 7(1.2%)               | 0.847   |
| Myalgia (N=5)      | 2(0.3%)               | 3(0.5%)               | 0.627   |
| Head ache (N=3)    | 2 (0.3%)              | 1 (0.2%)              | 0.583   |
| Diarrhoea (N=1)    | 0 (0.0%)              | 1 (0.2%)              | .309    |
| Joint pain (N=1)   | 1 (0.2%)              | 0 (0.0%)              | 0.325   |
| Sneezing (N=1)     | 1 (0.2%)              | 0 (0.0%)              | 0.325   |
| Body ache (N=1)    | 0 (0.0%)              | 1 (0.2%)              | 0.309   |

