**Sample size & statistical analysis:**

As per recently concluded our institutional pilot study, the incidence of COVID-19 was significantly ( $P = 0.033$ ) lower in the PEP group (10.6%) that received HCQ prophylaxis compared with the control group (19.5%). The total absolute risk reduction for the incidence of COVID-19 in participants received PEP with HCQ was  $-8.9\%$  points [13]. Anticipating at least 20% incidence of COVID-19 in control group as compared to 10% incidence rate in PEP group the total sample size will be around 400 (200 each group), when there will be 80% (power) chance of detecting a significant difference between the two groups at a one-sided 0.05 significance level ( $\alpha$ -error of 5%). Anticipating 10% dropout we will try to recruit total 440 participants for the study. However as per protocol, after following strict inclusion and exclusion criteria the final sample size for the data analysis may reduce further. Final power of the study may be recalculated after getting actual response/outcome at the end of the clinical trial through post-hoc statistical power analysis. Randomization will be done with the help of computer generated random number in a block randomization pattern in a block of 10 patients (5:5). Randomization and treatment concealment will be done by the pharmacologist. The data will be managed in data base system through Microsoft Excel and statistical analysis will be performed by SPSS 21.0 version. The parametric data will be

analyzed by paired or unpaired “t”-test and the binominal/categorical endpoints will be analyzed with non-parametric chi-square test with yet’s correlation and the proportions will be compared by Fisher’s exact test. The relative risk (RR) and number needed to treat (NNT) will be determined for the safety and risk assessment. The p-value less than 0.05 will be considered statistical significant (95% CI).

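### The optional post-hoc power recalculation would only restate the P value; read a null result from the relative risk and its interval, and reconcile the target of 440 with the 1,168 tabulated

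*Protocol*

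**What the plan says.** The sample-size paragraph in section 6 of the protocol rests on one scenario: "Anticipating at least 20% incidence of COVID-19 in control group as compared to 10% incidence rate in PEP group". From this, "the total sample size will be around 400 (200 each group"), with 80% power "at a one-sided 0.05 significance level". Allowing for loss, "Anticipating 10% dropout we will try to recruit total 440 participants for the study". The paragraph then warns that eligibility rules may lower the number analysed, and continues: "Final power of the study may be recalculated after getting actual response/outcome at the end of the clinical trial through post-hoc statistical power analysis". The recalculation is optional, and the effect size to be used in it is not given. The same section plans relative risk and number needed to treat, and a significance threshold of 0.05 with 95% CI.

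The results tables at the front of the document show larger numbers. eTable 1, limited to participants with RTPCR, is headed "Outcomes (N=1156") and splits into 587 control and 569 HCQ. eTable 2 has "Control group (N=594") and 574 in the HCQ group.

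**The concern.** Power is a property of a design at an effect chosen in advance. Once the observed effect is put in its place, the result is a one-to-one transform of the test statistic. It is low whenever the test is not significant and sits at about 50% when P is exactly 0.05. Quoted beside a null result, it suggests that the trial was too small, whether the confidence interval is narrow or wide. This matters because the protocol intends the data to inform national and international guidelines, and the tabulated primary result is null.

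The second matter is one of record. The protocol states one recruitment target and the tables show far more participants. A reader cannot tell what target was in force or how it was set.

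**Working it through.** **1. The plan's own figure.** For 20% versus 10%, 1:1 allocation and 80% power, the mean rate is 0.15 and

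n per arm = [1.96·√(2·0.15·0.85) + 0.8416·√(0.16 + 0.09)]² / 0.10² = 198.97, so 199 per arm (398 in total).

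This reproduces 400, but only two-sided. With 1.645 in place of 1.96 (one-sided, as written) n is 157 per arm. At 200 per arm, power is 80.2% two-sided and 87.8% one-sided. Figures below are two-sided unless stated.

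**2. Observed power as a function of P.** With z the normal deviate for the two-sided P, observed power = Φ(z − 1.96) + Φ(−z − 1.96).

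| Comparison (eTable 1) | HCQ | Control | P | z | Observed power |
|---|---|---|---|---|---|
| All COVID-19 | 23/569 | 24/587 | 0.968 | 0.040 | 0.027 + 0.023 = 5.0% |
| Definite COVID-19 | 16/569 | 21/587 | 0.460 | 0.739 | 0.111 + 0.003 = 11.5% (rounded from 11.45%) |
| Any result at the threshold | – | – | 0.05 | 1.960 | 50% |

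The uncorrected chi-square on these counts returns P=0.968 and 0.460, as tabulated. Only P enters the formula. One-sided, Φ(z − 1.645) gives about 5% and 18%; these differ, but P and the direction of the effect still fix them.

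**3. What the interval says.** The planned relative effect is 10%/20% = 0.5. eTable 1 gives 0.98 (0.55 to 1.77) for all COVID-19 and 0.78 (0.40 to 1.51) for definite COVID-19. The first lower limit is just above 0.5 and the second is below it.

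Check from the counts: RR = (23/569)/(24/587) = 0.99, with standard error of the log RR √(1/23 − 1/569 + 1/24 − 1/587) = 0.286, so 0.56 to 1.73. For definite cases, RR is 0.79 (0.41 to 1.49). The tabulated limits are slightly wider, but both sets give the same reading against 0.5.

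Risk difference for all COVID-19: 4.04% − 4.09% = −0.05 points, Wald 95% CI −2.3 to +2.2. Even if the drug prevented every case, the reduction at a 4.1% control rate could not exceed 4.1 points. That this interval excludes 10 points is therefore automatic.

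**4. Power that does carry information.** Take the planned halving at the tabulated control rate, 4.1% versus 2.05%. Power = Φ[(0.0205 − 1.96·s₀)/s₁], where s₀ and s₁ are the pooled and unpooled standard errors.

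- 200 per arm: s₀ = 0.01726, s₁ = 0.01723; Φ(−0.774) = 22% (one-sided 32%).
- 587 and 569: s₀ = 0.01018, s₁ = 0.01011; Φ(0.054) = 52% (one-sided 64%).

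Exact enumeration of the uncorrected two-sided test gives 21.5% and 52.9%. With Fisher's test, also named in the protocol, it is 13.6% and 49.3%.

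**5. Numbers of participants.** 594 + 574 = 1,168 (eTable 2) and 587 + 569 = 1,156 (eTable 1). 1,168/440 = 2.65.

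The 4.1% is the rate among the 587 tested controls. Among all 594 it lies between 24/594 = 4.0% and 31/594 = 5.2%, depending on the 7 who were not tested.

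**The case against.** The sentence is permissive and names no effect size. It could mean power at the planned effect with the observed control rate, which is not a function of P. That is fair. The point applies to the reading that the wording most naturally invites, and the ambiguity is itself a reason to rewrite it. It is also fair that the tables report relative risks with intervals and no post-hoc power, so no misreading has occurred in the text at hand.

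Four stronger readings are tempting and are not supported.

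- **That post-hoc power is the plan's answer to a wrong 20% control rate.** The protocol does not offer it for that purpose. The sentence follows a remark that the analysed number may shrink.
- **That the interval rules out the planned effect because it excludes 10 points.** As shown above, that exclusion is automatic at a rate near 4%. On the relative scale the evidence is borderline for one endpoint and open for the other.
- **That a blinded check of the event rate is wrongly missing.** Such a rule may sit in a statistical analysis plan that is not shown, and with results already tabulated it could no longer be applied.
- **That outcome data by arm drove the growth beyond 440.** Nothing in the document says so. The trial is described as double blind, with randomisation and concealment held by the pharmacologist.

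**Conclusion.** The point holds in a limited form. If computed at the observed effect, the recalculated power adds nothing to P: 5.0% and 11.5% for the two tabulated comparisons. It would not show that the relative-risk interval narrowly excludes a halving for all COVID-19 and includes it for definite COVID-19. Power at the pre-specified halving is a different and usable figure: about 22% with 200 per arm and about 53% with the numbers tabulated, against the 80% stated for 20% versus 10%. These rest on a 4.1% control rate from the RTPCR subset, a planned relative effect of 0.5, and an uncorrected two-sided 5% test.

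The gap between 440 and 1,168 is a real mismatch in the text at hand and needs a documented explanation. No conclusion about its cause follows. The stated primary comparison is unaffected, so this is a change that should be made rather than a fatal flaw.

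**What to change.** 1. Delete the sentence on post-hoc power. State instead that a non-significant primary result will be interpreted from the relative risk, with the risk difference, and its 95% CI, read mainly on the relative scale against the planned halving (RR 0.5).
2. If a power statement is kept, define it as power at the pre-specified relative effect with the observed control rate, and state the test and its sidedness.
3. Reconcile the target of 440 with the 1,168 participants in eTable 2 and the 1,156 with RTPCR in eTable 1. Give the target actually used, the date and basis of any change, and whether those who decided were blind to outcome by arm.

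Items 1 and 2 cost only wording; item 3 needs a look-up in the trial's records. None needs further participants or alters the type I error.

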**The following ethical considerations will be adhered to during the study:**

1. Patients will be enrolled in the study after full informed consent has been taken. The patients will have the right to quit the study at any point in time during the study and no compulsion will be exerted on them.
2. In case the patient is unable to consent due to poor neurological status, informed consent will be taken from a close relative available at that time. Patient/legal representative will be informed about the aim and method of the study, investigations that will be conducted on him/her, possible adverse effects associated

with the treatment modality under study and will have full right to refuse any investigation at any point in time during the study even after he/she has signed the consent and he/she will be excluded from the study.

4. The patient, irrespective of whether enrolled, will receive treatment as per the standard protocol followed in the Emergency Department of PGIMER, Chandigarh. The patient will not be exposed to any additional risk or cost.

5. Confidentiality of data collected from contribution source or individual will be maintained.

6. In the publication of the results of this study, all efforts would be made to preserve the accuracy of both the positive and negative results of this study.

**7. Time line:**

Study will be carried out during December 2020 onward to March 2021 (ongoing pandemic). As it is an ongoing serious pandemic without any definitive therapeutic cure we will try to generate adequate data at earliest to achieve our objectives at earliest.

**8. Updated CV including publication of the principal investigator:**

Copy attached

**9. List of intramural project granted: Ongoing / No financial grant received from PGIMER**

- i) Title: Efficacy of Empirical Ciprofloxacin plus Metronidazole and Cefixime plus Metronidazole Therapy for the Treatment of Liver Abscess: A Randomised Controlled Clinical Trial (INT/IEC/2019/000516)

**10. List of extramural project granted: Completed/ Funded by Pharmaaz India Pvt. Ltd.**

Title: “A prospective, multi-centric, randomized, double-blinded, parallel, saline controlled phase II safety and efficacy study of PMZ-2010 as resuscitative agent for hypovolemic shock due to excessive blood loss to be used along with standard shock treatment.” (Ledger page No:2760)

## Study design

[figure not shown]

